***Institute of Food Research***

**BACKGROUND**

Epidemiological evidence suggests that consumption of cruciferous vegetables, such as broccoli, is associated with a reduced risk of many types of cancers, Kristal (2002). More recently, this association has been linked with a possible protection against cancer of the prostate, Giovannucci *et al* (2003). The mechanism of chemoprevention is as yet unknown. However, the health benefits have been attributed to a major class of phytochemicals found in cruciferous vegetables known as glucosinolates.

References to the genus *Brassica* date back to ancient civilisation when its species were noted for their pungency and medicinal application, Fenwick *et al* (1983). The pungent, bitter taste can be attributed to the breakdown products of glucosinolates. When cruciferous vegetables are eaten, glucosinolates hydrolyse during the processes of chopping, chewing and ingestion, to form isothiocyanates and indoles. Broccoli contains various glucosinolates, but the most predominant are glucoraphanin, a precursor of sulforaphane [4-methylsulfinylbutyl ITC] and a potent anti-cancer compound in *in vitro* and animal studies, and glucoiberin (a precursor of the less bioactive ITC iberin [3-methylsulfinylpropyl ITC]), Mithen *et al* (2000).

*Mechanisms of Chemoprevention*

There is evidence that sulforaphane (SF) exerts an anti-carcinogenic effect by up-regulating various anti-carcinogenic enzymes involved in the detoxification and excretion of carcinogens. ITCs also down-regulate potentially pro-carcinogenic enzymes, such as cytochrome P450 enzymes, and enzymes involved in inflammatory responses that are also thought to be associated with cancer progression, Verhoeven *et al* (1997). Many recent studies are focusing on the involvement of SF in cell signal transduction pathways to elucidate its role in chemoprevention, Surh (2003).

The health-beneficial effects of ITCs have been investigated for many years; early work used pure compounds in animal studies and there is a substantial body of evidence that ITCs are effective inhibitors of carcinogenesis in a variety of animal models, Hecht (2000). Further evidence using cell line models has shown SF to up regulate the expression of genes involved in cell cycle suppression. This results in the suppression of growth and multiplication in human cancer cells originating from the liver, colon and prostate in vitro, Hintze et al (2003), Gamet-Payrastre et al (2000), Chiao et al (2002).

*Enhancing the Glucosinolate Content of Broccoli*

As the potential anticarcinogenic activity of broccoli has been associated with the presence of SF, a conventional breeding programme was set up at the John Innes Centre, Norwich, to selectively enhance the level of SF in broccoli. There is a wild cultivar of broccoli, originating from mountain tops in Sicily, which contains naturally high levels of glucosinolate. This cultivar was crossbred with a regular cultivar to produce a hybrid with increased levels of anticarcinogenic glucosinolate. This cultivar was developed specifically for use in human clinical intervention trials to allow further understanding of the role of ITCs in chemoprevention, Mithen *et al* (2003).

There are very few human intervention studies investigating the physiological significance of the action of glucosinolates on human health. Thus there is a great need to study pharmacokinetics, biomarkers of exposure and biomarkers of effect, in living people, following consumption of broccoli. Only then can we begin to interpret and understand the complexity of the role of broccoli in chemoprevention.

A recent human study was funded by the Biological and Biotechnological Sciences Research Council (BBSRC) and Nottingham University and approved by Queen’s Medical Centre Nottingham University Hospital NHS Trust Research Ethics Committee. Currently in the process of publication, this study examined the effects of acute exposure to ITCs in blood, urine and gastric tissue after consumption of broccoli enriched with glucosinolate. The study addressed methodological problems of measuring ITC metabolites in plasma, the effects of Glutathione-S-Transferase (GST) genotype on ITC exposure and changes in gene expression in the gastric mucosa of volunteers following consumption of enriched and standard broccoli cultivars. This is the same broccoli that will be used in the study proposed here.

*Genotype and Chemoprevention*

Several epidemiological studies suggest a further protection against cancer amongst individuals who have a deletion of certain genes, such as GSTs. This gene family convert reactive electrophiles, by conjugation with glutathione, to compounds that can be excreted from the body more easily. Approximately 40% of the population have a homologous deletion of the GSTM1 gene resulting in a null genotype. There is evidence that these individuals may have a higher protection by ITCs against certain cancers. We wish to explore this association further by genotyping the study population for members of the GST gene family.

*Justification for Pilot Intervention Trial*

In order to elucidate the mechanisms of chemoprevention of ITCs it is necessary to conduct a long term human intervention of broccoli to compare chronic exposure to ITC-enriched broccoli with the results of the acute clinical trial conducted in Nottingham. We wish to target men who have been previously diagnosed with high-grade Prostatic Intraepithelial Neoplasia (PIN) at the Norfolk and Norwich University Hospital by histopathologists with a special interest in prostate diseases. These men are at high risk for developing invasive prostate cancer (85% by year 5) and undergo routine prostate needle biopsies at 6 monthly intervals post diagnosis. The samples required for the study are thus part of normal diagnostic procedure and would provide very little additional inconvenience for the volunteers. The men would normally receive no medication unless cancer is detected and as such we anticipate a high compliance with the dietary intervention.

Prostate biopsy tissue will be taken before and after intervention of either broccoli or peas. We are primarily interested in the effect of broccoli on gene expression. However, peas are a good control because they cause the same change to the volunteers’ dietary regimen as adding broccoli and because they contain negligible amounts of glucosinolates. There is epidemiological evidence that peas may also be beneficial in reducing prostate cancer risk, but by different pathways to SF mediated action, Key *et al* (1997).

The study will use changes in gene expression as the main biomarker of effect. RNA will be extracted from the tissue and hybridised onto Affymetrix arrays. We will use validated software to create a gene expression profile of functional clusters of genes that are perturbed by the broccoli intervention. Subsequent analysis of selected genes by RT-PCR will confirm any significant changes in gene expression.

**OBJECTIVES**

1. To compare changes in gene expression, following a 12-month intervention of either broccoli or peas in subjects with high-grade PIN.
2. To assess changes in Prostate Specific Antigen (PSA) levels in response to a 12-month intervention of broccoli or peas in the study population.
3. To determine the genotype of individuals for key polymorphic genes and relate them to observed changes in gene expression.

**HYPOTHESIS**

Long-term consumption of broccoli results in changes in gene expression that may contribute to a reduction in cancer development and progression.

**STUDY DESIGN**

The study will be led by [name] and [name] at the Institute of Food Research, Norwich, in collaboration with [name] and [name] at the Urology and Histopathology departments of the Norfolk and Norwich University Hospital (NNUH) NHS Trust. A flow chart of the overall study is given in figure 1.

This is a parallel, dietary intervention studying male patients with high-grade PIN. Patients will be matched by genotype and diet into two dietary groups: (i) consuming 400g ITC-enriched broccoli per week (n=20) or (ii) consuming 400g peas per week (n=20). The study will involve dietary monitoring and collection of blood, urine and prostatic biopsy samples in a 12-month dietary intervention period. The prostate biopsies and blood will be collected during routine endoscopies as part of normal diagnostic procedure for this group of patients. The urine samples will be additional to routine procedure. It is anticipated that the drop out rate for this study will be 40% due to the progression of high-grade PIN to prostate cancer within the 12-month study period.

*Figure 1. Study Design.*

**ROLLING RECRUITMENT**

Male volunteers aged 30-70 years recruited by consultant urologist at NNUH. Information sheets and letters of invitation given to volunteers

**INFORMATION EXCHANGE**

Interested volunteers will be referred to study scientist at IFR and invited to attend an interview at the Human Nutrition Unit for initial information exchange

**CONSENT AND BASELINE BLOOD SAMPLE**

Interested volunteers will give informed, signed consent at the HNU. Volunteers will complete a health questionnaire and provide a baseline blood sample

#### SAMPLES

See figure 2

**DIETARY ASSESSMENT 1**

Recruited volunteers will complete a 7-day food intake diary and receive instructions on how to complete a dietary score sheet. Volunteers will be given a demonstration on how to cook the vegetable portions in a steamer.

**CLINIC APPOINTMENT 1**

Sample collection

#### SAMPLES

See figure 2

#### Group Allocation

**BROCCOLI GROUP**

Eat 4x100g portions of broccoli per week for 12 months

**PEAS GROUP**

Eat 4x100g portions of peas per week for 12 months

**DIETARY INTERVENTION PERIOD 1 (6 MONTHS)**

Fill in dietary score sheet

**DIETARY ASSESSMENT 2**

7 day food intake diary (rolling week basis) at 3-4 months

##

**CLINIC APPOINTMENT 2**

Sample collection

#### SAMPLES

See figure 2

**DIETARY INTERVENTION PERIOD 2 (6 MONTHS)**

Fill in dietary score sheet

**DIETARY ASSESSMENT 3**

7 day food intake diary (rolling week basis) at 10-11 months

**CLINIC APPOINTMENT 3**

Sample Collection

#### SAMPLES

See figure 2

**Recruitment Policy**

Patients with high-grade PIN, aged 30-70 years will be identified and recruited by [name], consultant urologist at the NNUH. Following a verbal expression of interest in the study, [name] will send a letter (annex 1) with a volunteer information sheet (annex 2) inviting potential volunteers to take part in the study. Volunteers will return a reply slip to IFR, contact details of the study scientist ([name]) will be provided to all potential volunteers.

Volunteers will be matched by genotype into two dietary groups: (i) consuming 400g ITC-enriched broccoli per week (n=20) or (ii) consuming 400g peas per week (n=20). Volunteer recruitment will continue until a total of 40 men have completed the trial. It is envisaged that 17 patients will be recruited per group and that the drop out rate for this study will be 40% due to the progression from high-grade PIN to prostate cancer within the 12-month study period. Interested volunteers will be invited to an information exchange at the Human Nutrition Unit (HNU) at IFR where the study scientist will explain details of the trial and encourage the volunteers to ask any questions. During this consideration period the volunteers will not be contacted.

*Inclusion criteria:*

- Male
- Diagnosed with high-grade PIN
- Aged between 30 and 70 years
- Smokers and non-smokers

*Exclusion criteria:*

- Undergoing chemopreventative therapy
- Receiving testosterone replacement medicines
- Prescribed 5 reductase inhibiters
- Active infection requiring treatment
- BMI <18.5 or >35
- Unable to give informed consent to take part
- Diagnosed with diabetes

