Volunteers will be asked to exclude cruciferous vegetables from their diet 48 hours prior to each visit to the clinic to avoid acute effects. The types of vegetables to avoid will be indicated in the dietary diaries. Biopsies of the prostate will be taken before, during and after the 12-month dietary intervention. The collection of all biopsy samples will occur at the urology clinic at the NNUH during routine Trans Rectal Ultrasound (TRUS) guided endoscopies. Thus, the samples required for the study will be collected at the same time as samples required as part of normal medical care. All patients will receive an explanation of the TRUS procedure by their consultant prior to the examination and a standard information sheet (annex 8).

The consultant will examine the prostate with an ultrasound probe. This is inserted into the rectum and images on a screen guide the sampling needles into the prostate. A small amount of tissue (10-20mg) is removed from the gland with the needles. The procedure takes approximately 30 minutes. As part of normal clinical care eight prostatic biopsy samples are collected for histology, in addition, up to six biopsy samples will be collected for the broccoli, peas and PIN study. The consultant will note from which lobe (right or left) the samples were taken.

Samples will be immersed in RNA later at the point of collection and subsequently snap frozen in liquid nitrogen before being transported to the tissue bank at the NNUH. A member of the study team will collect the samples from the tissue bank and transport to IFR for analysis. Tissue bank information sheets will be read (annex 10) and tissue bank consent forms (annex 9) signed by all volunteers prior to the TRUS procedure and copies will accompany all tissue transported to IFR.

*Progression to Prostate Cancer*

It is estimated that 30-40% of the study population may develop prostate cancer during the 12-month intervention. Volunteers diagnosed with cancer will be given appropriate medical counselling and advised to withdraw from the study by letter (annex 11). All non-medical members of the study team will be guided by the clinicians as to the most appropriate course of action for these individuals.

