**Dietary Intervention**

After giving fully informed, written consent, the volunteers will be matched by genotype and cruciferous vegetable consumption. The diet diary will be used to define high (> 3 portions per week) or low (< 1 portion a week) habitual consumers of cruciferous vegetables. Volunteers will be divided into two dietary intervention groups accordingly.

1. The ‘peas’ group will be asked to consume an additional 4 portions (100g each) of peas per week as part of their normal diet.

2. The ‘broccoli’ group will be asked to consume an additional 4 portions (100g each) of a special variety of broccoli, selectively grown for its enhanced glucosinolate content, per week as part of their normal diet.

Volunteers will be asked to modify their diets for a total of 12 months. This is to enable us to detect any long-term changes in gene expression and to coincide with the routine TRUS examinations every 6 months. Volunteers can choose which day to eat the vegetables, but will be asked to keep a record of when the vegetables were eaten.

Should the volunteers wish to go on holiday during the 12-month period, they will not be expected to adhere to the intervention. We will ask the volunteers to inform us of their planned holiday dates so that we can keep a record. We will ask them to avoid booking holidays for more than four weeks at a time or two weeks either side of their visits to the clinic and not within a month of the final assessment.

*Supply of Vegetables*

The broccoli will be grown and harvested by Olga Ltd, Boston, Lincolnshire, and processed by Christian Salvesen, Bourne, Lincolnshire. The broccoli is a hybrid cultivar, conventionally crossed with a wild species that has an enhanced level of the glucosinolate called glucoraphanin (precursor of sulforaphane). Samples will be packaged into 100g portions and stored frozen at -18oC until cooked by the volunteer. Frozen peas will be bought from a supermarket. Both types of frozen vegetable will be delivered to the volunteers on a regular basis by a member of the study team or Polymek, a temperature controlled delivery service, at a time convenient to the volunteer. Should any volunteer not own a freezer, IFR will loan a PAT tested freezer to the volunteer for the duration of the study.

*Cooking Guidelines for Frozen Vegetables*

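### Recruitment closes only on the 40th completion, about a year after enough men are on study, and this trigger contradicts the 17 recruits per group envisaged in the next sentence

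*Protocol*

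**What the plan says.** The Recruitment Policy section of the protocol makes four statements about numbers, one after another:

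- Group sizes: "i) consuming 400g ITC-enriched broccoli per week (n=20) or (ii) consuming 400g peas per week (n=20".
- Closing rule: "Volunteer recruitment will continue until a total of 40 men have completed the trial".
- Forecast of recruits: "It is envisaged that 17 patients will be recruited per group".
- Dropout: "the drop out rate for this study will be 40% due to the progression from high-grade PIN to prostate cancer within the 12-month study period".

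Elsewhere:

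- Figure 1 describes recruitment as rolling. It gives no accrual rate, recruitment period or cap.
- Dietary Intervention sets the time to completion: "Volunteers will be asked to modify their diets for a total of 12 months".
- Sample Collection gives a range for progression: "It is estimated that 30-40% of the study population may develop prostate cancer during the 12-month intervention". Men diagnosed with cancer are advised to withdraw. Ethical Considerations also provides for their withdrawal.
- Sample Collection adds research tissue to the eight routine cores: "in addition, up to six biopsy samples will be collected for the broccoli, peas and PIN study". Biopsies are taken before, during and after the intervention.
- Sample Analysis assigns four cores per visit, two to arrays and two to RT-PCR.

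No sentence deals specifically with men who are part-way through when the 40th man completes.

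**The concern.** A closing rule has to act on something known when the decision to enrol the next man is made. Completion is known 12 months too late for that. While the team waits for the 40th completion, the rule tells it to keep consenting, allocating and taking research biopsies from men who cannot count towards the 40.

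The rule also does not fit the forecast beside it. A reader who plans on 34 recruits and one who follows the completion trigger would run trials of very different size. Two things are at stake: additional needle cores that the target does not need, and a protocol that does not settle how many men will be enrolled.

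**Working it through.** **Inputs from the protocol.** Target 20 completers per group, 40 in total. Dropout d = 0.40 (Recruitment Policy), with 30-40% progression in Sample Collection. Envisaged recruits 17 per group. Time to completion 12 months. Up to 6 research cores per visit, of which 4 are assigned in Sample Analysis.

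**Assumption.** Accrual rate r men per month. The protocol gives none, so 1 and 2 per month are shown for illustration only.

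**1. The protocol's own recruitment figure.** Recruits needed = completers / (1 - d).

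| Dropout | Per group | Total |
|---|---|---|
| 40% | 20/0.60 = 33.3, so 34 | 40/0.60 = 66.7, so 67 |
| 30% | 20/0.70 = 28.6, so 29 | 40/0.70 = 57.1, so 58 |

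The stated 17 per group is not reproduced. Taken forward, 34 men give 34 × 0.60 = 20.4 completers at 40% dropout and 34 × 0.70 = 23.8 at 30%. Fewer than 40 men cannot yield 40 completers at any dropout. Seventeen per group would match 10 completers per group (10/0.60 = 16.7), and 34 would match the number needed in one group rather than two. The protocol does not say how 17 was reached.

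**2. Men enrolled too late to count.** If the man who becomes the 40th completer starts at time t, the trigger fires at t + 12 months. Men starting in between number about 12r: 12 at r = 1, 24 at r = 2. Simulation of the rule gave means of 12 and 24 (5th to 95th percentile 7 to 18, and 16 to 32).

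**3. Research cores already taken from them when the trigger fires.** All 12r have had the baseline visit and about half (6r) the 6-month visit.

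- Upper bound, six cores per visit: 12r × 6 + 6r × 6 = 108r, or 108 at r = 1 and 216 at r = 2.
- Four assigned cores per visit: 12r × 4 + 6r × 4 = 72r, or 72 and 144.

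Both ignore withdrawals before 6 months.

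**4. How much over-enrolment is justified.** The chance of at least 40 completers from N men is a binomial tail, P(Bin(N, 1 - d) ≥ 40).

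| N enrolled | d = 0.40 | d = 0.30 |
|---|---|---|
| 58 | 0.10 | 0.63 |
| 67 | 0.57 | 0.97 |
| 75 | 0.90 | above 0.99 |
| 78 | 0.95 | above 0.99 |

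At 40% dropout a reasoned margin is therefore 75 - 67 = 8 to 78 - 67 = 11 men. The rule as written adds about 12r, whatever the dropout.

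These chances concern the total. For at least 20 in each group, with 75 men split 37 and 38 and dropout independent of group, the chance at d = 0.40 is P(Bin(37, 0.6) ≥ 20) × P(Bin(38, 0.6) ≥ 20) = 0.818 × 0.862 = 0.71.

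**The case against.** The strongest reply is that a completer target under 30-40% attrition simply means that dropouts are replaced, and that the forecast of 34 recruits points to a shortfall, not a surplus. The second half is right about the forecast, and the contradiction is part of this point. It does not rescue the trigger. The forecast is only an expectation, while the trigger is the operative instruction and would carry recruitment past 34 with no stated limit.

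A reader might infer that every man recruited in the last year is surplus. The documents do not support that. Who will progress is unknown at enrolment, some over-enrolment is needed, and at 1 man per month the 12 extra men are close to the 8 to 11 that a planned margin would add. Accrual that slow, however, means about 67 + 12 = 79 months to the 40th completion. Nor is the whole last year's intake still on the diet at the trigger, since men who progress leave.

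A reader might also infer that the final sample could be chosen after results are known. That is speculative. The trigger counts completions, no interim look is described, Dietary Intervention sets 12 months for all volunteers, and Statistical Analysis says that all array data are analysed.

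Finally, one might read the total of 40 as permitting unequal groups. The sentence just before it gives 20 per group, so that reading is strained, although a per-group wording would remove the doubt.

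**Conclusion.** The point holds in a limited form. The closing rule acts about 12 months too late, and it cannot stand beside 17 recruits per group with 40% dropout: those figures give about 20 completers (24 at 30%), not 40.

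The contradiction rests on the protocol's own figures alone. The delay follows from the rule, rolling entry and a 12-month intervention. The size of the excess does not come from the documents. It is about 12 men at an assumed 1 per month and 24 at 2 per month, and part of it is legitimate insurance against dropout. The core counts are illustrative too, and 108r is an upper bound.

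**What to change.** Replace the trigger sentence and the 17-per-group sentence with one rule that acts on men enrolled. It should contain:

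- **Closure.** Recruitment closes when men who have completed, plus men still on study multiplied by their expected completion fraction, reach 20 in each group. Start from the protocol's own 30-40% dropout and update it from observed withdrawals. The protocol gives only a 12-month figure. Applying it to men already part-way through understates their chance of completing, so it errs towards a few extra men.
- **Expected enrolment.** About 29 to 34 recruited per group, plus a stated margin. For example, about 75 in total gives a 90% chance of at least 40 completers at 40% dropout. If the aim is 20 in each group with similar assurance, the margin must be larger (see the 0.71 above).
- **Men on study at closure.** They continue the planned intervention, subject to the withdrawals already described in Sample Collection and Ethical Considerations, and are included in the analysis.

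The cost is a short protocol amendment and a running tally by group. The downside is that the final number of completers may fall a few above or below 40, which a pilot with no power target can accept.

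### The envisaged 17 recruits per group cannot yield the 40 completers that the protocol sets as its recruitment target; at 40% dropout they yield about 20

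*Protocol*

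**What the plan says.** The protocol's Recruitment Policy section makes three statements about numbers within a few lines.

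- Group size: n=20 in each arm, for peas "consuming 400g peas per week (n=20") and likewise for broccoli.
- When recruitment ends: "Volunteer recruitment will continue until a total of 40 men have completed the trial".
- The recruitment forecast and expected loss: "It is envisaged that 17 patients will be recruited per group and that the drop out rate for this study will be 40" per cent, with the loss attributed to progression to prostate cancer.

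The Study Design section repeats the group size, "consuming 400g ITC-enriched broccoli per week (n=20"), and the loss: "It is anticipated that the drop out rate for this study will be 40% due to the progression of high-grade PIN to prostate cancer". It does not mention 17 and does not say whether n counts men allocated or men completing.

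The paragraph on progression to prostate cancer (under Sample Collection) and the Ethical Considerations section both put progression over the 12 months at 30-40%. Nothing in the protocol explains the 17 or reconciles it with 40 completers.

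**The concern.** The forecast, the dropout rate and the completer target are linked by simple arithmetic, and they do not fit together. A reader who takes the forecast at face value plans for 34 men. A reader who takes the completer rule at face value has to plan for about twice that number.

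The difference matters beyond tidiness. Each man is asked for up to six study cores on top of the eight taken in routine care, at each of three sampling visits. How many men will be asked to do this is a basic fact for anyone approving or running the study. The number of completers also fixes the precision of the 12-month comparison between groups. That comparison is the main yield of a pilot meant to supply data for sizing later studies.

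**Working it through.** **Inputs, all from the protocol**

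- Completer target: 40 in total, with n=20 per group (Recruitment Policy; n=20 also in Study Design).
- Envisaged recruitment: 17 per group, so 2 × 17 = 34 in total (Recruitment Policy).
- Dropout d: 40% (Study Design and Recruitment Policy).
- Progression, the stated cause of dropout: 30-40% (progression paragraph and Ethical Considerations).

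**Step 1. Do 17 recruits per group give 20 completers?** Completers = recruited × (1 − d).

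| Dropout | Completers per group | Total |
|---|---|---|
| 40% | 17 × 0.6 = 10.2 | 20.4 |
| 30% | 17 × 0.7 = 11.9 | 23.8 |
| 0% | 17 | 34 |

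The target of 40 is not reached in any row. No dropout rate can turn 17 recruits into 20 completers.

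**Step 2. What recruitment does the target need?** Recruited = completers / (1 − d), rounded up within each group.

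- At 40%: 20/0.6 = 33.3, so 34 per group, 68 in total. (Rounding the total once, 40/0.6 = 66.7, gives 67; two equal groups need 68.)
- At 30%: 20/0.7 = 28.6, so 29 per group, 58 in total.

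The forecast of 17 is half the number needed at the protocol's own dropout rate. The common mistake of multiplying by 1 + d does not explain it either: 20 × 1.4 = 28.

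**Step 3. Does reading n=20 as men allocated help?** No. Seventeen recruited is fewer than 20 allocated, and 20 × 0.6 = 12 completers per group, 24 in total, still misses 40.

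**Step 4. Can the origin of 17 be recovered?** Not uniquely. Ten completers per group gives 10/0.6 = 16.7, rounded up to 17. The correct 34 per group, mistaken for a total and halved, also gives 17. So does 12 × 1.4 = 16.8, rounded up. These routes imply different intended designs.

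**Step 5. Effect on precision if 17 per group is a true limit.** With equal groups and the same standard deviation, the standard error of a between-group difference is proportional to 1/√n. The ratio for 10.2 against 20 completers per group is √(20/10.2) = 1.40.

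**The case against.** The strongest reply is that the protocol has an operative rule, and it is counted in completers: recruitment goes on until 40 men have finished. The 17 is only envisaged. A reader might infer that the trial will close at 17 per group and end with half its men, or that its final size cannot be known. The text does not support that, because nothing in it stops recruitment at 17. This part of the reply stands, and it limits the finding to a forecast that is incompatible with the rule. It does not remove the finding: if the rule governs, the forecast is too low by a factor of two, and the protocol does not say so.

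A second reply is that this is a pilot for which the Statistical Analysis section declines a power calculation. That is a fair reason not to attach a detectable difference for a single gene to either group size, since the protocol specifies no such test and screens more than 47,000 transcripts. It does not excuse group sizes that contradict each other.

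Other stronger readings should also be resisted:

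- The 17 cannot be said to be left over from a different, smaller trial. Step 4 shows that other slips give the same number.
- A reader might infer that no room is left for loss from other causes. But 40% is the top of the stated progression range, and recruiting until 40 complete would absorb further loss.
- Effects on vegetable supply or array budget cannot be sized, because the protocol gives no quantities for them.

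A separate analysis plan, if there is one, would not cure the problem. The incompatible figures are stated in the protocol.

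**Conclusion.** The point holds as an arithmetic contradiction between neighbouring statements in Recruitment Policy. The envisaged recruitment leads to about 10 completers per group (about 20 in total) at the stated dropout, against a target of 20 per group (40 in total). It falls short even if nobody drops out. Meeting the target needs about 34 per group at 40% dropout, or 29 per group at 30%.

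This rests only on the protocol's own figures and equal groups, and it survives either reading of n. The standard-error ratio of 1.4 further assumes the same variability in both scenarios. It applies only to the 12-month comparison, since men lost after the mid-point visit can still contribute the 6-month biopsy. Which figure is the intended one cannot be settled from the document; the sponsor has to say.

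**What to change.** Give one consistent set of figures in Study Design and Recruitment Policy, and state in both that n counts completers. There are two ways to do it.

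1. **Keep the rule of 40 completers.** Replace the envisaged 17 with about 34 per group (68 in total) at 40% dropout. If a range is wanted, 29 per group (58 in total) is the figure at 30%. The wording is cheap, but it acknowledges that twice as many men must be recruited as now forecast.
2. **Keep 17 per group, if that is the real limit.** Restate the target and the recruitment stopping rule as about 10 completers per group (20 in total), and change n=20 accordingly. The cost is precision: the standard error of the 12-month between-group comparison is about 1.4 times that with 20 per group.

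Neither option needs a change to the assessments or to the analysis model.
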